### Intervention

Eight 90-min exposure sessions will be carried out by therapists who are well trained in cognitive behavioral therapy (CBT), including exposure exercises, and in the current study protocol. Protocols in this study are based on standardized protocols of exposure with response prevention in social phobia [39] and in panic disorder with agoraphobia [40]. The protocols consist of therapist-assisted exposure in vivo to fear-provoking thoughts and situations, coupled with response prevention treatment (e.g. not leaving the feared situation or using safety behaviors), tailored to idiosyncratic symptoms of the patients. After every therapy session homework is given, resulting in patients doing at least 8 exposure exercises per week.

Two hours prior to the exposure treatment sessions the study medication is administered. Timing of administration is based on a study by Englund et al. [41], indicating Tmax at 3 h 45 min after administration with high plasma levels from 2 h onwards. Therefore, taking the medication 2 h before the start of the session results in relatively stable CBD levels during the entire session.

The eight sessions that are part of the study protocol are not expected to be sufficient for most patients to achieve remission, but this allows sufficient room to investigate whether CBD strengthens therapy response relative to placebo. After the eight sessions in the study protocol patients can continue treatment as needed without further administration of study medication.

### Assessments

Response to treatment will be assessed at baseline (T0), at mid-treatment (T2), post-treatment (T4) and at 3 and 6 months’ follow-up (T5 and T6 respectively). During treatment, a short assessment is done at each therapy session. Table 1 provides an overview of the measures that are used at each time point. The primary endpoint of this study is the clinical outcome post-treatment (at assessment T4). The other measurements are aimed at the time course of the effect. The mid-treatment and per session assessments are specifically aimed at examining the possibility of a quicker and/or stronger effect of exposure with CBD as opposed to placebo, whereas the follow up measurements allow evaluation of potential long term beneficial effects of CBD. Furthermore, preceding the first and last treatment session with medication administration (T1 and T3 respectively) several secondary measures will be used to study the mechanism underlying acute effects of CBD. Also, blood samples from these assessments will be used to determine CBD plasma levels.

**Table 1 Tab1:** Overview of assessments

Measure	Assessment	T0	T1	T2	T3	T4	T5	T6	Treat-ments
SCID	Diagnosis	x							
General patient characteristics	Demographic information	x							
Clinical background	Therapy history	x							
CTQ	Childhood trauma	x							
AQ	Autism quotient	x							
FQ	Presence and severity phobic symptoms	x		x		x	x	x	x
BAI	Anxiety severity	x		x		x	x	x	x
CGI	Clinical global impression								x
SUDS	Degree of habituation and extinction								x
BDI	Depression	x		x		x	x	x	
BSQ	Somatic symptoms	x		x		x	x	x	
EQ5D	Quality of life	x		x		x	x	x	
Tic-P	Loss of work and productivity plus health care costs	x		x		x	x	x	
SPAI	Social phobia and anxiety severity	x		x		x	x	x	
LSAS	Social anxiety severity (SOC PHOB)	x		x		x	x	x	
PDSS	Panic disorder severity (PD + AGO)	x		x		x	x	x	
MI	Mobility inventory (PD + AGO)	x		x		x	x	x	
ACQ	Agoraphobia severity (PD + AGO)	x		x		x	x	x	
Fear conditioning task	Acquisition and extinction of fear learning	x	x		x				
Blood	CBD level, DNA, epigenetics		x		x				

Questionnaires that are only assessed for a specific diagnosis are specified between brackets (panic disorder with agoraphobia = PD + AGO, social phobia = SOC PHOB). T0 = Baseline, T1 = First medication administration, T2 = Mid treatment, T3 = Last medication administration, T4 = Post treatment, T5 = Follow up (3 months), T6 = Follow up (6 months), Treatments = All 8 therapy sessions. *SCID* Structured Clinical Interview for DSM disorders axis I, *CTQ* Childhood Trauma Questionnaire, *AQ* Autism spectrum Quotient, *FQ* Fear Questionnaire, *BAI* Beck Anxiety Inventory, *CGI* Clinical Global Impression, *SUDS* Subjective Units of Distress Scale, *BDI* Beck Depression Inventory, *BSQ* Bodily Sensations Questionnaire, *EQ5D* EuroQol, *Tic-P* Trimbos and iMTA questionnaire on Costs associated with Psychiatric illness, *SPAI* Social Phobia and Anxiety Inventory, *LSAS* Liebowitz Social Anxiety Scale*, PDSS* Panic Disorder Severity Scale, *MI* Mobility Inventory, *ACQ* Agoraphobic Cognitions Questionnaire

### Outcome measures

#### Primary outcome

The primary outcome measure is the Fear Questionnaire (FQ; [42]) which will be administered at every time point (T0-T6) and at every treatment session.

The *FQ* is a part of a standard self-report questionnaire measuring avoidance, the complete form also includes one specific main target phobia, a global phobia rating, and five associated anxiety and depression symptoms (not included in this study). The version of the FQ employed here consists of 15 items asking about the most common phobias rating avoidance using a nine-point scale from ‘0: would not avoid it’ to ‘8: always avoid it’. The score reflects the level of avoidance, with a total score range from 0 to 120. Three subscores can also be derived using the sum of 5 items, concerning Agoraphobia, Blood injury phobia and Social phobia.

#### Secondary outcomes

##### Clinical questionnaires

Various secondary outcome measures are used to further explore the effect of CBD augmentation on general clinical and specific disorder-related symptoms. Baseline scores on these questionnaires will be used to develop clinical determinants of the effect from augmentation with CBD. All secondary clinical questionnaires are administered at baseline, mid- and post-treatment and follow up assessments.

The *Beck Anxiety Inventory* (BAI; [43]) is a 21-item self-report instrument that assesses the overall severity of anxiety. Respondents rate how much each symptom bothered them the past week on a 4-point scale, ranging from 0 (not at all) to 3 (severely, I could barely stand it). The BAI is scored by summing the ratings for all the 21 symptoms to obtain a total score ranging from 0 to 63. Whereas avoidance (measured using the FQ) is a highly relevant clinical construct, restricting analysis to just this aspect may overlook impact on other symptoms of anxiety, such as physiological changes, that may not have a direct effect on behavior as measured by the FQ. Therefore, we have chosen to use the BAI as most important secondary outcome, which is why it is also administered at every treatment session with the FQ.

The *Beck Depression Inventory-II* (BDI-II; [44]) is a 21-item self-report instrument that is the most widely used to assess the presence and/or intensity of depressive symptoms. Similar to the BAI, symptoms are scored on a 4-point scale resulting in total scores ranging from 0 to 63.

The *Body Sensations Questionnaire* (BSQ [45]) is a 17-item self-report instrument assessing fear for bodily sensations associated with autonomic arousal. Items are rated on a 5-point scale, total scores range from 17 to 85.

The *Social Phobia and Anxiety Inventory* (SPAI; [46]) is used to assess specific somatic symptoms, cognitions and behavior across a range of potentially fear-producing situations. The original SPAI has two subscales, Social phobia (32 items) and Agoraphobia (13 items). A shorter SPAI-18 has been developed assessing only the Social Phobia scale [47]. In this study the SPAI-18 is combined with the original Agoraphobia subscale, resulting in 31 items. Thirteen items require separate ratings concerning either four different social situations or physiological and cognitive questions. Mean scores are calculated for these items based on the 7-point scale ranging from 1 (never) to 7 (always). To obtain the score the number of items is subtracted from the summed item scores. The maximum score for the SPAI-18 is 108, and for the Agoraphobia scale 78.

Only during the treatment sessions the *Clinical Global Impression* (CGI; [48]) and *Subjective Units of Distress* (SUDS; [49]) are administered. The CGI consists of 2 items, measuring illness severity and improvement. The items are rated on a 7-point scale by the therapist, with the severity scale ranging from 1 (normal) to 7 (amongst the most severely ill patients), and the improvement scale ranging from 1 (very much improved) to 7 (very much worse). Each component is rated separately, there is no total score [50]. The SUDS are used during exposure to measure within-session extinction. Before and after the exposure in vivo exercise percentage of fear and credibility of thoughts about the exercise are rated by the patient [51].

Besides the broader clinical questionnaires, diagnosis-specific questionnaires are only administered to patients with the diagnosis in question. Questionnaires pertaining to the diagnosis of panic disorder with agoraphobia:

The *Panic Disorder Severity Scale* (PDSS; [52]) is a 7-item clinician-administered instrument assessing severity of panic disorder and monitoring treatment outcome. Items are rated on a 5-point scale which ranges from 0 to 4, total scores are calculated by summing the scores for the items resulting in a range of 0 to 28.

The *Mobility Inventory* (MI; [53]) is a 27-item self-report instrument for the measurement of agoraphobic avoidance behavior in specific situations. These situations are rated both when patients are accompanied and when they are alone. Items are rated on a 5-point scale which ranges from 1 (never) to 5 (always), the score is calculated by averaging the items.

The *Agoraphobic Cognitions Questionnaire* (ACQ; [45]) is a 14-item self-report instrument assessing thought concerning negative consequences of experiencing anxiety. Each item is rated on a 5-point scale ranging from 1 (never occurs) to 5 (always occurs), total scores are calculated by averaging the items. Specifically, catastrophic thoughts typically noted during exposure to anxiety-provoking experiences are used, making it highly relevant for the assessment of therapy success.

Questionnaire pertaining to the diagnosis of social phobia:

The *Liebowitz Social Anxiety Scale* (LSAS; [54]) is a self-report instrument with 24 items measuring both fear and avoidance across a number of social situations. Fear scale ratings range from 0 (no fear) to 3 (severe fear), avoidance ratings also range from 0 to 3 and are based on percent of time avoiding the situation (0 = never, 1 = occasionally (10%), 2 = often (33–67%), and 3 = usually (67–100%). The LSAS is divided in two subscales, related to performance anxiety (11 items) and social interaction (13 items).

All clinical questionnaires have been shown to have adequate reliability and validity (ACQ [55], BAI [56], BDI [57], BSQ [58], FQ [59], LSAS [60], MI [53], PDSS [61], SPAI [47]), except for the CGI [62] which is advised to be used in accordance with other validated questionnaires, which are used in this study.

##### General patient characteristics

Demographic information such as age, gender, education, employment, nationality and marital status will be collected using a general demographic questionnaire at baseline. Current use of drugs and medication is assessed with a short questionnaire. Additional questions are asked concerning the clinical background, e.g. treatment history, and the Childhood Trauma Questionnaire [63] is administered.

##### Experimental assessment of fear learning

To explore whether capacity for fear and extinction learning at baseline impacts the effect of CBD, and whether treatment with CBD has impact on improvements in extinction learning after treatment, an experimental fear conditioning and extinction task will be used to assess the capacity to acquire and extinguish conditioned fear [30]. At baseline, this task will investigate the acute effect of CBD on extinction learning, a second extinction phase with the same conditioned stimuli as at baseline is administered 2 h after the first ingestion of the medication. This additional fear extinction phase is administered 1 to 2 weeks after administration of the baseline fear conditioning task. Finally, post-treatment the same fear conditioning task will be administered, with minor adaptations to minimize previous learning effects (e.g. with different conditioned stimuli). With this post-treatment task, changes in rate of extinction due to treatment is compared between the CBD and placebo groups.

##### Genetics

Profiling of phobic patients based on genetic variance will be done to examine potential factors that have impact on the effect of exposure therapy and on the effect of CBD augmentation. In general, we expect more benefit of CBD augmentation for individuals with genetic profiles associated with lack of spontaneous extinction. More specifically, for the impact on CBD augmentation, genetic variance in CNR1 [20], FAAH [31, 64] and genes related to treatment response in phobic disorders [32], will be analyzed.

##### Cost effectiveness

The documentation of (non-)medical costs and productivity loss will be collected to assess cost-effectiveness of CBD-augmented psychotherapy. Both cost effectiveness-questionnaires are administered at baseline, mid- and post-treatment and follow up assessments.

The *Treatment inventory of costs in Psychiatric patients* (Tic-P [65]) is a self-report questionnaire consisting of two parts, medical resource, including volume of mental and general health care utilization (direct medical costs), travel to and from health care providers (non-medical costs), and productivity loss, generated by absence from paid work (indirect costs). Corresponding costs are calculated by multiplying the volumes by the corresponding reference unit prices [66].

The *EuroQol five dimensions* (EQ5D [67]) is a 5-item self-report instrument which is the most commonly used generic health status measurement. The items have five response categories from no problems to incapacity/extreme problems. Additionally, a visual analogue scale (VAS) is used to rate their health on a scale ranging from 0 (worst possible health) to 100 (best possible health).

### Statistical analysis

#### Treatment augmentation

Data concerning the primary and secondary outcome measures will be analyzed by comparing the scores on the measurement scales using mixed modeling, with medication (CBD vs. placebo) and time (time points: baseline, mid-treatment, post-treatment and follow-ups). Analyses are conducted according to the intention-to-treat principle, i.e. all patients who have completed the baseline assessment are included in the analyses. Furthermore, also a ‘completers only’ analysis will be done including just the participants who have completed the treatment and participated in all measurements (T0-T6).

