### Sample size

The CBD and placebo groups will each include 36 patients. The sample size is aimed at detection of a Cohen’s D effect size of 0.6, based on effect sizes found in previous published studies on the augmentation of exposure with d-cycloserine [37]. This sample size has been calculated using G*power version 3.0.10 [38], with a repeated measures design for two groups with two measurements, an envisioned effect size of 0.6 Cohen’s D, error probability of 0.05, power of 0.8 and correlation among repeated measurements of 0.6 based on previous clinical data.

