### Randomization and blinding

The randomization (CBD or placebo) is conducted by an independent statistician using a computer algorithm, stratifying for study location and diagnosis (panic disorder with agoraphobia or social phobia). Patients are allocated to one of the medication groups after baseline measurements according to the order of patients in the stratum. Investigators, research assistants, therapists and participants will be blinded with respect to randomization. The capsules containing the different medications are identical in appearance except for filling which is either CBD or lactose (placebo). An independent data manager can break the randomization code in case of pregnancy, allergic reactions or any severe inexplicable symptoms. Apart from these circumstances, unblinding will not be done until after the last patient has completed the last follow up measurement.

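### Baseline FQ is a level of time in the primary model with no stated baseline adjustment; fixing a common baseline mean would recover precision at T4 at no cost

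*Protocol article*

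**What the plan says.** The Treatment augmentation section of the protocol article analyses the primary and secondary outcomes by mixed modelling, with medication and "time (time points: baseline, mid-treatment, post-treatment and follow-ups") as factors. Baseline is thus one of the outcome time points. The section does not mention a medication-by-time interaction, a baseline covariate, a constraint on the baseline means, or the contrast that gives the treatment effect. Its intention-to-treat set is everyone who completed the baseline assessment.

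Three other sections bear on the point:

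- Assessments: "The primary endpoint of this study is the clinical outcome post-treatment (at assessment T4").
- Randomization and blinding: "Patients are allocated to one of the medication groups after baseline measurements".
- Sample size: the calculation uses "an envisioned effect size of 0.6 Cohen’s D" and a "correlation among repeated measurements of 0.6 based on previous clinical data".

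The Patient profiling section does list clinical state at baseline as an independent variable, but only for the exploratory predictor models.

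**The concern.** Because allocation follows the baseline assessment, any observed arm difference in FQ at T0 is chance. A model that gives each arm its own baseline mean spends information on estimating a difference known to be zero. With complete data, its T4 effect relative to baseline is simply the arm difference in change scores.

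That contrast is valid, but it subtracts the whole of the baseline difference. At a correlation of 0.6 and equal SDs, only about 0.6 of that difference is expected to carry through to T4. Two things follow for the primary endpoint of a 72-patient trial: a larger standard error than necessary, and an estimate that moves with chance imbalance at baseline. Randomization is stratified by location and diagnosis, not by FQ severity, so the design does not remove such imbalance.

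**Working it through.** **Inputs** (Sample size section): d = 0.6, error probability 0.05 (taken as two-sided), power 0.80, two groups, two measurements, correlation ρ = 0.6, 36 per arm. Assumptions of this check: equal SDs at T0 and T4 (set to 1), 0.6 is the T0–T4 correlation, and data are complete.

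**Reproducing the plan's figure.** The repeated-measures between-factors calculation with f = d/2 = 0.3, m = 2 and N = 72 has noncentrality λ = N f² m / (1 + (m − 1)ρ) = 72 × 0.09 × 2 / 1.6 = 8.1. With F(1, 70) this gives power 0.801; N = 70 gives 0.790. The stated 72 is reproduced. The within-between interaction version with f = 0.3 would give N = 20, so it is not what was used. The between-factors variance factor is (1 + 0.6)/2 = 0.80.

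**Variance factor of the T4 effect** (the variance of the effect is 2/n times this factor):

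- Free baseline means, T4-minus-baseline contrast: 2(1 − ρ) = 2 × 0.4 = 0.80
- Common baseline mean, or baseline as covariate: 1 − ρ² = 1 − 0.36 = 0.64
- Ratio: 0.80/0.64 = 2/(1 + ρ) = 1.25

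Generalized least squares on a five-time-point model (T0, T2, T4, T5, T6) also gives 1.25. It does so under compound symmetry, and under an unstructured matrix with a T0–T4 correlation of 0.6. At 36 per arm under compound symmetry the variances are 0.0444 (free) and 0.0356 (constrained).

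**Power at d = 0.6, 36 per arm** (noncentral t, noncentrality 0.6/√(2v/36)):

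| Analysis | v | Noncentrality | Power |
|---|---|---|---|
| Change contrast, free baseline means | 0.80 | 2.85 | 0.80 |
| Common baseline mean or covariate | 0.64 | 3.18 | 0.88 |

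The normal approximation gives 0.812 and 0.889. On that approximation, 80% power needs 35 per arm with the change contrast and 28 with baseline adjustment.

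**Range of the inflation under other assumptions:**

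| Assumption | Extra variance of the change contrast |
|---|---|
| ρ = 0.5 | +33% |
| ρ = 0.7 | +18% |
| ρ = 0.8 | +11% |
| ρ = 0.6, SD at T4 0.8 times that at T0 | +66% |
| ρ = 0.6, SD at T4 1.2 times that at T0 | +9% |

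The last two rows use (1 + s² − 1.2s)/(0.64s²), where s is the SD ratio. If the baseline means were free and the effect were read as the raw arm difference at T4, the factor would be 1.00, and the loss 1/0.64, or +56%.

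**Chance imbalance.** The standard error of the baseline arm difference is √(2/36) = 0.24 SD, so a difference of 0.2 SD is unremarkable. It shifts the change contrast by (1 − 0.6) × 0.2 = 0.08 SD relative to the adjusted estimate.

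**The case against.** The strongest reply is that the article does not state separate baseline means. A reader might infer them from the two factors listed, since they are the usual default, but the text leaves the parameterization open. Nor is listing baseline under time an error in itself: a model with a common baseline mean also has T0 as a time point, and it loses nothing. Such detail can properly sit in an analysis plan that is not shown. All of this stands, so the point is conditional. It remains worth making because the article does say how baseline enters, and following that sentence in the ordinary way leads to the less efficient contrast.

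A reader might also infer that the primary analysis is biased or the trial underpowered. The documents do not support either. The change contrast is unbiased over randomization; the shift computed above is conditional on an observed imbalance. At ρ = 0.6 the factor behind the planned sample size happens to equal the change-score factor, both 0.80. So 36 per arm still gives about 80% power before any dropout.

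A larger benefit could be claimed by assuming missing T4 data. The article gives no dropout rate, it plans continued assessment of patients who stop the intervention, and a mixed model uses their other visits. No such figure is relied on here.

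**Conclusion.** The point holds as a free improvement. The plan makes baseline an outcome time point and names neither an adjustment nor a common baseline mean, although randomization guarantees equal true means at T0.

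If the baseline means are left free, the T4-minus-baseline contrast carries about 25% more variance than necessary, and power is about 0.80 where 0.88 is available from the same patients. These figures rest on the protocol's d = 0.6, on 0.6 being the T0–T4 correlation (the article says only that it holds among repeated measurements), on equal SDs, and on complete data. The direction is the same across the ranges examined; the size is not. If the analysis already constrains the baseline means, the loss is zero and only the wording needs completing.

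**What to change.** State in the analysis plan that T0 stays in the outcome vector, that both arms share a common baseline mean, that medication effects are estimated separately at T2, T4, T5 and T6, and that the primary result is the medication contrast at T4. This agrees with the existing list of time points and keeps every patient with a baseline assessment, as the intention-to-treat rule requires.

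A near-equivalent alternative models the post-baseline scores with baseline FQ and its interaction with time as covariates. It drops patients who have only a baseline value, which conflicts with that rule, so the common-mean version is preferable.

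Apply the same to the BAI and the other scales measured at T0. The cost is wording only: baseline FQ is already scheduled for everyone before allocation, and neither the sample size nor the visit schedule changes. The choice should be fixed before unblinding.
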